*Metformin* has pleiotropic effects but is generally considered to serve as a net “insulin sensitiser” in conditions of ectopic adiposity with insulin resistance; in addition, it raises AMPK activity, and the circulating concentrations of Growth-and-Differentiation Factor 15 (GDF15), a peptide hormone that reduces hepatic steatosis and raises intestinal glucose utilization thereby promoting weight loss [59–61]. Metformin was first approved in 1959, and since then several FDCs have been approved for the treatment of type 2 diabetes as first- and/or second-line therapies [62]. Worldwide, metformin is the drug most widely prescribed for the treatment of type 2 diabetes in adults and in children older than 10 years; its use has significantly increased in younger children and adolescents without diabetes, including for early maturation and PCOS in girls [37–41, 63]. Extensive experience has been gathered over the last 60 years related to the clinical use and safety of metformin [64]. In 2001, the European Medicines Agency (EMA) issued a favorable benefit-risk ratio for metformin that outlines its safety in humans [62]. The main side effects are gastrointestinal symptoms (~10%), that usually resolve after therapy start [64]. Lactic acidosis has been only described in cases of renal, cardiac and hepatic failure, or after intentional overdose [65]. A decrease of vitamin B12 serum levels may occur after long-term treatment but appears to be of no clinical relevance [66]. The combination of spironolactone and metformin is not associated with a higher incidence of adverse events compared to low-dose spironolactone or metformin in monotherapy [50]. Based on the EMA Summary of Product Characteristics (https://www.medicines.org.uk/emc/product/594/smpc#POSOLOGY), the dose range studied for metformin in clinical trials is mainly 200–850 mg/day, with a maximum of 2000 mg/day. Hence, the proposed dose of metformin (425 mg/day) will be in the lower recommended range, assuming that the weight of pubertal girls aged 8–9 years will be >25 kg [67].

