### Outcomes {12}

#### Primary outcome

The primary outcome is annualized bone age (BA) advancement over the on-treatment year. A hand and wrist X-ray of the left hand will be obtained at the treatment start and after 1 year on treatment. BA advancement will be measured by an automated/blinded method called BoneXpert (Visiana, Denmark) [1].

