## Data collection and management

### Plans for assessment and collection of outcomes {18a}

#### Collection of outcomes

*Baseline evaluation (time 0):* will include the clinical visit to collect clinical variables: height, weight, BMI, Tanner stage, waist and hip circumference and their ratio (WHR), SBP, DBP, a hand and wrist X-ray (to assess bone age), MRI (to assess abdominal fat partitioning and hepatic fat) and blood sampling in the fasting state (to assess endocrine-metabolic and inflammation variables and safety markers). Dietary habits will be also recorded through a standard questionnaire (Kidmed).

*Evaluation on treatment (time 6 months and 1 year):* a clinical visit with the same parameters collected at baseline, an abdominal MRI, and a blood sample extraction (to assess endocrine-metabolic and inflammatory variables and safety markers) will be performed after 6 months and after 1 year on treatment. Dietary habits, study adherence, acceptability of the tablet, and adverse events will be also recorded. After 1 year of treatment, a hand and wrist X-ray will be performed for bone age assessment.

*Evaluation post-treatment (time 2 years):* will include a clinical visit 1 year after treatment discontinuation, collecting the same parameters as at time 0, 6 months, and 1 year; in addition, an abdominal MRI scan and a blood sampling (to assess endocrine-metabolic and inflammation variables and safety markers) will be performed. Dietary habits, study adherence, acceptability of the tablet, and adverse events will be also recorded. Six months later a phone call will be made to ascertain the presence or absence of menarche.

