#### Assessment of outcomes

*Bone age:* A hand and wrist X-ray of the left hand will be taken at the Radiology Department either at HJT or HSJD, at treatment start and after 1 year on treatment. At each center, bone age will be determined with the same BoneXpert programme [version 3; February 2021 (Visiana, Denmark)] [38]. This method will yield bone ages by Greulich & Pyle (GP) and by Tanner-Whitehouse 2 (TW2). Bone age maturation will be annualized by calculating the ratio between the increase of BA over the increase in CA (ΔBA/ ΔCA) [38].

*Clinical characterization:* Clinical variables will be obtained during the clinical visits with the pediatric endocrinologist at HJT and HSJD. The same investigator at each center will assess the clinical variables at times 0, 6 months, 1 year, and 2 years. Halfway the second post-treatment year, the girls will be contacted by phone to discuss the absence or timing of menarche.

*Blood sampling:* 23 mL of peripheral blood in a fasting state will be drawn in the early morning at each clinical center, at baseline (time 0), after 6 months on treatment, after 1 year on treatment, and 1 year off treatment. Blood samples will be stored (at −80 °C) at the Pediatric Endocrinology lab (IDIBGI) and at the Metabolic Endocrinology lab (IRSJD) until analyses.

*Endocrine-metabolic variables analysis:*

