## Statistical methods

### Statistical methods for primary and secondary outcomes {20a}

The statistical analyses will be performed with the SPSS program, version 23.0 (SPSS, Chicago, Illinois, USA). The analysis of quantitative variables of independent groups will be performed using ANOVA for repeated measurements in models adjusted for potential confounding variables. The association between BA, clinical variables, endocrine-metabolic, and imaging variables will be sought by correlation and multiple regression analysis. A statistical analysis will be done by intention to treat and another with the patients who have completed follow-up. *p*<0.05 will be considered statistically significant.

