### Methods in analysis to handle protocol non-adherence and any statistical methods to handle missing data {20c}

An intention-to-treat analysis will be performed including all participants randomized to either placebo or mini-spiomet, ignoring non-compliance, protocol deviations, withdrawal, and anything that happened after randomization. If necessary, for the withdrawn participants, the missing data will be filled with the data of previous visits.

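### The carry-forward rule has no usable value for the primary outcome: a girl who withdraws before month 12 gets a bone-age ratio of 0, in the direction of benefit, or an undefined one

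*Protocol article*

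**What the plan says.** Four statements in the protocol article bear on this.

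- **Endpoint.** Under Primary outcome: "The primary outcome is annualized bone age (BA) advancement over the on-treatment year". Under Assessment of outcomes it is obtained by "calculating the ratio between the increase of BA over the increase in CA", that is, ΔBA/ΔCA.
- **Films.** Primary outcome and Assessment of outcomes place the hand film at treatment start and after 1 year on treatment. Collection of outcomes describes the 6-month and 1-year visits together and names the film for the later one only: "After 1 year of treatment, a hand and wrist X-ray will be performed for bone age assessment".
- **Missing data, section {20c}.** "An intention-to-treat analysis will be performed including all participants randomized to either placebo or mini-spiomet", whatever happens after randomisation. Then, if necessary, "for the withdrawn participants, the missing data will be filled with the data of previous visits". No outcome is exempted and no criterion is given for when filling is necessary.
- **Analysis sets, section {20a}.** "A statistical analysis will be done by intention to treat and another with the patients who have completed follow-up". Neither is named as primary.

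The Sample size section plans on ratios of about 1.20 (untreated) and 1.00 (treated), SD 0.2 in each, and allows for loss of up to one third of the girls.

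**The concern.** Carry-forward needs an earlier on-study value of the same quantity. For the primary outcome there is none between baseline and the final reading. Filling the 1-year bone age from the previous film means filling it with the baseline film, which says that the skeleton did not mature at all. In this trial slower maturation is the benefit, so the filled value is an extreme response and not a cautious one.

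Two things are at stake. If withdrawal is equal in the arms, a cluster of zeros inflates the SD and shrinks the difference, so a true effect is likely to be missed. If withdrawal is unequal, the arm that loses more girls appears to mature more slowly, whatever the drug does. The sample size calculation assumes that girls without a 1-year film simply do not contribute; section {20c} brings them back as zeros.

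**Working it through.** **Inputs.** Means 1.20 and 1.00, SD 0.2, power 90%, 21 per arm raised to 32, loss up to one third (Sample size). Two-sided 5% level: section {20a} uses p < 0.05, so the 0.05% printed under Sample size is read as 0.05.

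**1. The plan's own figure.** n per arm = 2 × (1.96 + 1.2816)² × 0.2² / 0.20² = 21.01, against 21 stated. Normal-approximation power with 21 per arm is 0.900 (0.885 by the t-test). Inflation: 21 / (1 − 1/3) = 31.5, so 32. The plan's reasoning is reproduced: 21 girls per arm with two films carry the power.

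**2. What the rule gives.** ΔBA = baseline BA − baseline BA = 0.
- Age taken at the nominal year: ratio = 0/1 = 0. Distance from the planned means: 1.20/0.2 = 6 SD and 1.00/0.2 = 5 SD.
- Age carried forward too: ratio = 0/0, undefined.

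**3. Equal withdrawal, planned effect true.** If a proportion p withdraws at random and is set to 0, the arm has mean (1 − p)μ and SD = √[(1 − p) × 0.2² + p(1 − p)μ²]. For p = 1/3 and μ = 1.20: mean 0.80, SD = √(0.0267 + 0.3200) = 0.59. Power is from a simulated two-sample t-test, 32 per arm, 40,000 replicates, with each girl's withdrawal random.

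| Withdrawal per arm | Means (placebo, active) | Difference | SDs (placebo, active) | Power |
|---|---|---|---|---|
| 0 | 1.20, 1.00 | 0.20 | 0.20, 0.20 | 97.6% |
| 5% | 1.14, 0.95 | 0.19 | 0.33, 0.29 | 68% |
| 10% | 1.08, 0.90 | 0.18 | 0.41, 0.35 | 47% |
| one third | 0.80, 0.67 | 0.13 | 0.59, 0.50 | 16% |

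The SD rises roughly 1.5-fold, 2-fold and 2.5- to 3-fold. If the loss of one third is instead exactly 11 of 32 in each arm, power is about 0%.

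**4. Unequal withdrawal.** The splits are assumptions; the article gives only an overall ceiling of one third.
- No true effect (1.20 in both arms), 10% on active and 0% on placebo: spurious benefit 1.20 × 0.10 = 0.12.
- No true effect, one third on active and one sixth on placebo: 1.20 × (1/3 − 1/6) = 0.20, the whole design effect.
- Planned effect true, 8 of 32 lost on placebo and 3 of 32 on active: means 1.20 × 24/32 = 0.900 and 1.00 × 29/32 = 0.906. The true benefit of 0.20 disappears.

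False-positive rates are less stable than the bias. With random counts, the first two cases reject in 27% and 31% of trials. With counts fixed near the same splits, 0 vs 3 rejects in 18% and 5 vs 10 in about 4%, although the spurious difference in the last is still 1.20 × 5/32 = 0.19.

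**5. Without the zeros.** If withdrawal is unrelated to outcome, 21 observed girls per arm give 0.885 by the t-test (0.90 by the plan's formula), and 29 vs 24 give 0.94.

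**The case against.** - **The rule is conditional and does not mention bone age.** One can also say that a ratio has no earlier value, so there is nothing to carry and it stays missing. That is a possible reading, but then section {20c} offers no way to include all randomised girls in the primary analysis. Each reading ends in 0, in 0/0, or in no value.
- **A completers analysis is planned and needs no filled values.** True. A reader might infer that carry-forward alone settles the trial's primary result; the article does not support that, because it ranks neither analysis. For the same reason the completers analysis does not cure the fault.
- **Later films could exist.** Section {17b} invites withdrawing families to an end-of-study visit, but specifies no film there. The 6-month visit is said to repeat the baseline parameters, but the film schedule is explicit in three places.
- **More withdrawals on active treatment.** A reader might infer a predictable false benefit from the gastrointestinal effects of about 10% quoted for metformin and the symptoms listed in section {11b}. The article does not support that. Section {11b} concerns stopping medication, the fill rule concerns withdrawn participants, and a girl who stops tablets can still have her 1-year film. The metformin effects are also described as usually resolving. Excess withdrawal on active is possible, but its size is not established, and the bias can run the other way.
- **Tanner stage, height and hormones.** These have 6-month values, so carry-forward there is the ordinary kind and a lesser matter, outside this point.
- **The detailed analysis plan may differ.** It may, but this is a stated rule that does not work for the stated endpoint, not an omission.

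**Conclusion.** The point holds. As written, the only missing-data method for the intention-to-treat analysis turns a withdrawn girl's primary outcome into 0, which is 5 to 6 SD below the planned means on the side of benefit, or leaves it undefined. With equal random withdrawal and the planned effect true, power falls from about 98% to about 68%, 47% and 16% at 5%, 10% and one third per arm. This defeats the sample size section, which expects about 90% power at the largest of these losses. This part needs no assumption about imbalance between arms.

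With unequal withdrawal the estimate is biased in either direction, by 0.12 to 0.20 in the two no-effect examples. Those sizes rest on assumed splits, and no single false-positive rate should be quoted because it depends on whether counts are treated as random or fixed.

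The calculations use a two-sample t-test on the ratio. The adjusted repeated-measures ANOVA in section {20a} was not simulated, but with baseline bone age carried to 1 year it would also see zero change for these girls.

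**What to change.** In section {20c}:

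1. Exclude bone age and ΔBA/ΔCA from carry-forward.
2. Name the primary analysis: a comparison by randomised arm of all girls with an observed 1-year film, including those who stopped medication, adjusted for baseline variables already collected.
3. Add a sensitivity analysis that imputes the missing ratios, including one version in which missing treated girls are given the placebo rate.

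The cost is a short rewrite of {20c}, a matching line in {20a} saying which analysis is primary, and slightly more analysis work. No new girls or films are needed. The price is that the primary analysis relies on missing ratios being missing at random given the adjustment variables; the placebo-rate version shows how far the result depends on that.

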### Plans to give access to the full protocol, participant-level data and statistical code {31c}

The full protocol, participant-level dataset, and statistical code will be provided on demand.

## Oversight and monitoring

### Composition of the coordinating center and trial steering committee {5d}

This is a multicenter study that will be held in (1) Josep Trueta Hospital (HJT) and Institut d'Investigació Biomèdica de Girona [name] (IDIBGI) (Girona) and (2) Sant Joan de Déu Hospital (HSJD) and Institut de Recerca Sant Joan de Déu (IRSJD) (Esplugues, Barcelona). The coordinating center is HJT-IDIBGI. The trial steering committee will be composed by the principal investigator of each institution ([name] and [name]) and the research coordinators ([name] and [name]) and will meet once per semester to coordinate and supervise all the tasks. A group of nurses, pediatricians, and researchers at each institution will provide day-to-day support for the trial.

### Composition of the data monitoring committee, its role and reporting structure {21a}

ADKNOMA Health Research SL is a Clinical Research Operator (CRO) that will provide support during the trial development process as a clinical regulatory specialist and will be responsible of the trial monitoring and data audit, regulatory issues, pharmacovigilance, and coordination of security activities.

### Adverse event reporting and harms {22}

The nature, severity, treatment, and outcome of any potential adverse event will be recorded by the clinical investigator seeing the patient at each center during the clinical visits (at 6 months, 1 year, and 2 years) or at the phone call contacts (at 3 and 9 months).

All adverse events and harms, whether expected or unexpected, will be collected in a non-systematically way asking the patient about their health, and will be coded according to MedDRA (CTCAE v4).

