#### Specific

To determine whether pharmacological intervention with a low-dose combination of spironolactone (25 mg/day), pioglitazone (3.75 mg/day), and metformin (425 mg/day) within a single tablet (mini-spiomet) over 1 year in “mismatch” girls with early puberty, reduces hepatic and visceral fat significantly more than placebo, as assessed by MRI.To ascertain whether in girls treated with mini-spiomet, the reduction of hepatic and visceral fat associates to (1) a greater deceleration of bone maturation [as evaluated by Δ bone age (BA)/Δ chronological age (CA) ratio over 1 year]; (2) a slower pubertal *tempo* (as judged by the progression of Tanner stage); and (3) more normal levels of insulin, IGF-I, inflammation markers, sex steroids, HMW-adip, CXCL14, and GDF15, as compared to girls who received placebo.To assess whether the benefits of mini-spiomet on hepato-visceral fat and endocrine-metabolic markers on-treatment are still detectable 1 year after treatment discontinuation.To evaluate the tolerance and safety of mini-spiomet over 1 year (by assessing safety parameters), as well as the acceptance of the tablet (through a specific visual questionnaire).

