### Criteria for discontinuing or modifying allocated interventions {11b}

In all participating girls, safety markers [blood count, circulating levels of alanine transaminase (ALT), aspartate transaminase (AST), gammaglutamyltransferase (GGT), thyroid-stimulating hormone (TSH), urea, creatinine, electrolyte panel, vitamin B12, folic acid] will be assessed at treatment start, after 6 months and 1 year on treatment, and after 1 year off treatment, as well as upon reporting any adverse events. Glucose blood levels <65 mg/dL and a progressive increase of creatinine, urea, transaminase or potassium levels, will be a reason for discontinuing the medication. In addition, the existence of signs and/or symptoms of hypoglycemia, the appearance of a persistent skin rash, abdominal pain, persistent nausea and/or vomiting, headaches, sinusitis, and severe bacterial infections, will be also a reason for discontinuation. In those cases, hepatic and renal function will be periodically monitored until the disappearance of the symptoms or the normalization of the altered parameters.

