#### Secondary outcomes

◦ Clinical variables: weight, height, BMI, waist and hip circumference and their ratio (WHR), systolic blood pressure (SBP), diastolic blood pressure (DBP), and Tanner stage [4].◦ Endocrine-metabolic variables:fasting glucose, insulin, HOMA-IR [5], IGF-ILH, FSH, testosterone, androstenedione, SHBG, FAI and estradioltriglycerides; total, low- and high-density lipoprotein (LDL and HDL) cholesterolultra-sensitive C-reactive protein (usCRP), GDF-15, HMW-adip, CXCL14.◦ Safety markers: blood count, circulating concentrations of alanine transaminase (ALT), aspartate transaminase (AST), gammaglutamyltransferase (GGT), thyroid-stimulating hormone (TSH), urea, creatinine, electrolyte panel, vitamin B12, folic acid.◦ Abdominal fat partitioning (subcutaneous visceral area) and intrahepatic fat by MRI.◦ Dietary habits, tablet acceptability, study adherence, adverse events.

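### Adverse events are to be collected by an unsystematic health question, which weakens ascertainment of the symptoms that a secondary outcome and part of the discontinuation rule depend on

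*Protocol article*

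**What the plan says.** Adverse event reporting and harms {22} covers "All adverse events and harms, whether expected or unexpected" and says that they "will be collected in a non-systematically way asking the patient about their health". The investigator records nature, severity, treatment and outcome "during the clinical visits (at 6 months, 1 year, and 2 years) or at the phone call contacts (at 3 and 9 months").

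Three other parts of the protocol article rely on these data:

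- **Objective.** Objectives {7}, Specific, includes: "To evaluate the tolerance and safety of mini-spiomet over 1 year (by assessing safety parameters"), together with acceptance of the tablet.
- **Outcome.** Secondary outcomes lists "Dietary habits, tablet acceptability, study adherence, adverse events". The end of Assessment of outcomes, under {18a}, has all outcomes compared between groups at the stated time points.
- **Discontinuation and extra tests.** Criteria for discontinuing or modifying allocated interventions {11b} gives as reasons for stopping "the existence of signs and/or symptoms of hypoglycemia, the appearance of a persistent skin rash, abdominal pain, persistent nausea and/or vomiting, headaches, sinusitis". The last item on that list is severe infection of bacterial origin. The same section adds safety bloods whenever an adverse event is reported.

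The background section on the pilot studies says of metformin: "The main side effects are gastrointestinal symptoms (~10%), that usually resolve after therapy start".

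**The concern.** This is a stated choice of method, not a detail left out. A general question about health tends to find fewer symptomatic events than a list that names them, and what it finds depends on who asks, how, and who answers. Section {22} names the patient as the person asked. She is 8.0 to 9.5 years old at entry, and the parent is not mentioned. The first scheduled contact for recording events on treatment is the 3-month phone call. A gastrointestinal complaint that settles soon after starting may be over by then.

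Two things are at stake. The first is the tolerance part of the safety objective: with 32 girls per arm, a modest loss of cases takes counts from few to very few. The second is the symptom part of the discontinuation rule and the event-driven blood draws, which can operate only on symptoms that someone has learned of. No section says that the listed symptoms are asked about in the same way at each contact or at both centers.

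**Working it through.** No figure in the protocol is in dispute here, so there is none to reproduce. The check has three steps.

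**1. Which safety data depend on questioning**

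| Component | Section | Depends on questioning? |
|---|---|---|
| Laboratory markers at start, 6 months, 1 year, and 1 year off treatment | {11b} | No |
| Laboratory reasons for discontinuation (glucose, creatinine, urea, transaminase, potassium) | {11b} | No for scheduled draws |
| Symptom reasons for discontinuation | {11b} | Yes |
| Extra safety bloods after a reported event | {11b} | Yes |
| Adverse events as a secondary outcome | Secondary outcomes, {22} | Yes, for symptomatic events |

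**2. Size of the loss in one arm (illustration)**

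Inputs: n = 32 per arm (Trial design {8}); true rate p = 0.10, the metformin gastrointestinal figure in the background; captured share s, which is an assumption because the document gives none.

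Expected recorded cases = n·p·s. Chance of recording none = (1 − p·s)^n. The chance of at least three is the binomial tail with n = 32 and probability p·s.

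| s | Expected cases | P(none) | P(3 or more) |
|---|---|---|---|
| 1.00 | 32 × 0.10 = 3.2 | 0.90^32 = 0.03 | 0.63 |
| 0.50 (assumed) | 32 × 0.05 = 1.6 | 0.95^32 = 0.19 | 0.21 |
| 0.25 (assumed) | 32 × 0.025 = 0.8 | 0.975^32 = 0.44 | 0.05 |

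**3. Effect on the comparison between arms**

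Sequence generation {16a} plans 16 girls per arm at each center. Let the centers capture shares sA and sB, and assume that a center captures alike in both arms and that the true rate in an arm is the same at both centers. An arm with true rate p then records 16·p·sA + 16·p·sB = 32·p·(sA + sB)/2 cases. The factor (sA + sB)/2 is the same in both arms, even when the centers differ. For example, with sA = 0.75 and sB = 0.25 (assumed), the factor is 0.50 in each arm.

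With a common factor s, the recorded ratio is (s·p1)/(s·p2) = p1/p2, which is unchanged. The recorded difference is s·(p1 − p2), which shrinks, so power falls. For an assumed true contrast of 20% against 5%, 32 per arm and two-sided 5%, the normal approximation is

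power = Φ{[d − 1.96·√(2·p̄(1 − p̄)/32)] / √[(p1(1 − p1) + p2(1 − p2))/32]},

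with p1, p2, their mean p̄ and d = p1 − p2 all on the recorded scale:

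- s = 1.00: 20% against 5%, d = 0.150, power 0.44
- s = 0.50: 10% against 2.5%, d = 0.075, power 0.23
- s = 0.25: 5% against 1.25%, d = 0.0375, power 0.14

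The approximation is rough at counts this small, and power is low even with full capture. The direction is what matters.

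**The case against.** The strongest defence has five parts.

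- **Events are asked about.** An investigator asks about health at scheduled contacts, and Strategies to improve adherence {11c} repeats that contact every 3 months serves to monitor adverse events. This stands: it would be wrong to infer that nobody asks, or that everything rests on what a child volunteers unprompted. Parents are not named, but neither are they excluded.
- **The prompts may be in the full protocol.** An article commonly leaves visit forms to it. That would answer an omission. It does not answer a positive statement that collection is non-systematic for all events, expected ones included.
- **The comparison between arms is sound.** A reader might infer that uneven prompting makes laboratory findings and discontinuations non-comparable. The documents do not support that. Tablets are indistinguishable ({11a}), only the pharmacy knows the allocation during treatment ({17a}), and allocation is balanced within each center ({16a}). Uneven prompting between centers is possible, but the protocol does not show it.
- **The example does not fit the whole discontinuation rule.** That rule speaks of persistent nausea and/or vomiting and persistent rash, so missing a brief early episode does not defeat those items. This stands. The gastrointestinal example bears on tolerance as an outcome.
- **A checklist has a cost of its own.** Section {11b} lists abdominal pain and headaches without a clear grade or duration. A bare yes/no list could turn everyday complaints into grounds for discontinuation or extra blood draws. This stands, and the change below takes it into account.

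**Conclusion.** The point holds for symptomatic events only. The stated collection method is weaker than the protocol's own uses of the data require: a secondary outcome compared between groups, the tolerance part of an objective, and the symptom part of the discontinuation rule. Scheduled laboratory safety data are unaffected, and nothing here touches the primary outcome.

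The likely effect is lower recorded rates and less power to see a difference, not bias toward one arm. The size depends wholly on the captured share, which the document does not give; the figures for half and a quarter are assumptions. The 10% rate is a general metformin figure, not one for this combination at this dose, and the calculation leaves out background complaints.

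A reader might conclude that a clean tolerability profile is likely whatever the truth. The figures do not support that: even at quarter capture, the chance of recording no gastrointestinal case is 44%, below one half. The supported statement is that effects the protocol itself expects can be missed or under-counted in arms of this size, and that this is cheap to avoid.

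**What to change.** In Adverse event reporting and harms {22}, keep the open question and follow it at each existing contact (3, 6, 9, 12 and 24 months) with a short fixed checklist of the symptoms already named in {11b}. Ask it of the girl and the parent in identical words at both centers, and record severity and onset and stop dates. Report solicited and volunteered events separately by arm.

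Before the checklist is used, reconcile {22} with {11b}: the sponsor should state how a positive answer relates to the discontinuation rule and to the event-driven blood draws. No clinical threshold is proposed here.

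The cost is a one-page form and a few minutes at contacts already planned. Event counts will rise in both arms, including background complaints, for which the placebo arm provides the reference. If the two sections are not reconciled first, extra blood draws or discontinuations may follow.

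A minor separate point: {22} runs MedDRA and CTCAE together. It should say that terms are coded with MedDRA and severity is graded with CTCAE.
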